## Abstract

**Background:**

Over 50% of newly diagnosed patients with breast cancer are aged ≥65 years. Due to age-related factors and the presence of comorbidities, these patients are particularly vulnerable to developing cardiac toxicity associated with cancer treatments, which may lead to suboptimal interventions and undertreatment, resulting in poorer health outcomes, quality of life (QoL) deterioration, and increased health care costs. Given the underrepresentation of older patients with breast cancer in clinical trials and the increasing recognition of the impact of psychosocial and behavioral factors on cardiovascular disease onset, broader and interdisciplinary studies are required to develop new and innovative best practices for this clinical population.

**Objective:**

Using an innovative eHealth approach combining the CARDIOCARE (An Interdisciplinary Approach for the Management of the Elderly Multimorbid Patient with Breast Cancer Therapy Induced Cardiac Toxicity—grant agreement 945175) mobile app and technologically advanced wearable devices (ie, the Garmin Venu SQ watch and Polar H10 sensor), the CARDIOCARE prospective study pursues a twofold aim: (1) testing the effectiveness of the CARDIOCARE mobile app to monitor and assess the intrinsic capacity and QoL of older patients with breast cancer and evaluating the CARDIOCARE eHealth interventions’ effectiveness on these parameters and (2) developing a holistic, patient-centered risk prediction model specific for the detection of cardiotoxicity before it clinically emerges.

**Methods:**

This prospective and multicentric study involves 6 clinical and 5 technical partners across Europe. In total, 750 older patients with breast cancer (aged ≥60 years) are assigned to either the standard practice or enhanced monitoring group, with only patients in the latter receiving access to eHealth psychological, behavioral, and functional interventions implemented on the CARDIOCARE eHealtHeart app. Patients will be recruited in 6 clinical centers and will undergo clinical procedures to collect multimodal data, including clinical data, cardiac imaging, biochemical and psychological biomarkers and omics, intrinsic capacity, and QoL indicators measured at baseline (T0) and every 3 months up to 12 months (T5).

**Results:**

CARDIOCARE is a project funded by Horizon 2020, and enrollment started in May 2023. As of October 17, 2024, a total of 50% (375/750) of the target number of patients had been recruited.

**Conclusions:**

The CARDIOCARE prospective study will contribute to developing new best practice guidelines for managing older patients with breast cancer and multimorbidity while preserving their intrinsic capacity and improving their QoL. Furthermore, the CARDIOCARE mobile app and the wearable devices will allow clinicians to identify trajectories across the cardiotoxicity disease continuum and thus intervene in a preventative way among patients at higher risk. Such a health care approach will also benefit the health care system, which currently spends almost 40% of its resources on patients aged >60 years, with long-term care and hospital admissions being the primary cost drivers.

**Trial Registration:**

ClinicalTrials.gov NCT06334445; https://clinicaltrials.gov/study/NCT06334445

**International Registered Report Identifier (IRRID):**

DERR1-10.2196/63455

## Introduction

### Background

Over 50% of newly diagnosed patients with breast cancer are aged >65 years and are particularly vulnerable to the cardiotoxic effects of cancer treatment due to multiple comorbidities and age-related risk factors [1]. The cumulative effect of risk factors in the older patient with breast cancer resembles a “snowball effect” in which baseline age-related risk factors and cancer-related changes are further exacerbated by cancer therapy–induced cardiotoxicity [2,3], resulting in severe multimorbid conditions and increased mortality. Underestimating the cardiotoxicity risk in this vulnerable population may lead to inappropriate interventions and undertreatment, contributing to poorer health outcomes, quality of life (QoL) deterioration, and increased health care costs. Considering that older patients with cancer are systematically underrepresented in clinical trials [1], there are currently limited means to effectively address the complex needs of these patients and their caregivers, often resulting in undertreatment and suboptimal health outcomes, with negative consequences to patients’ QoL [1]. Therefore, in line with the World Health Organization’s view that health is a state of complete physical, mental, and social well-being [4], broader, interdisciplinary, and patient-oriented clinical trials are urgently needed to provide new evidence-based best practices for managing older patients with breast cancer. To date, the most effective approach to minimize cardiotoxicity is baseline risk stratification and appropriate follow-up during treatment for the early detection of cardiotoxicity.

Moreover, psychological conditions such as depression, distress, and anxiety—often observed in patients with cancer after diagnosis [5]—can increase the risk of cardiovascular complications [6]. Similarly, people presenting negative affectivity and social inhibition are at higher risk of cardiovascular disease as such negative affectivity is significantly associated with higher systolic and diastolic blood pressure [7,8]. Similarly, prolonged exposure to stressful life circumstances may predict subsequent hypertension and cardiovascular disease [3]. Therefore, the Integrated Care for Older People guidelines recommend a comprehensive cardiological assessment as well as a detailed evaluation of patients’ intrinsic capacity. Intrinsic capacity refers to the composite of all the physical and mental capacities that an individual can draw upon at any point in time. It encompasses a wide range of abilities, including cognitive, emotional, physical, and sensory functions, that together influence an individual’s functional ability and QoL as they age [9]. This holistic and patient-oriented approach aims to establish new best practices for the management of older patients with cancer at risk of cardiotoxic effects associated with oncological treatments [10].

### Novelty and Study Aim

Multimodal retrospective data have been retrieved from existing databases in 5 of the 6 clinical centers belonging to the CARDIOCARE consortium and involved in the observational prospective cohort study (hereafter referred to as the *prospective study*)—the Bank of Cyprus Oncology Centre (BOCOC) in Cyprus, the European Institute of Oncology (IEO) in Italy, Karolinska University Hospital (KSBC) in Sweden, National and Kapodistrian University of Athens (NKUA) in Greece, and University of Ioannina (UOI) in Greece—to develop a risk prediction model for cardiotoxicity in the older adult population with breast cancer to be refined and validated through the CARDIOCARE prospective study. In the prospective study, the cardiotoxicity risk prediction model will be enriched with novel biochemical, omics (metagenomics, micro-RNAs, and single-nucleotide polymorphisms), and psychological markers to better assess how patients’ intrinsic capacity (physical and mental) and QoL are affected by cancer and anticancer treatments and how they influence the risk of developing cardiac toxicity. So far, no extensive studies have allowed for the collection of all the necessary data to conduct a meaningful assessment of the intrinsic capacity and QoL of older patients with breast cancer.

It has to be considered that patients recruited in the CARDIOCARE clinical study receive different types of systemic therapy, including chemotherapy, targeted therapy, immunotherapy, and hormonal therapy. They also receive different types of local treatment comprising surgical treatment (wide local excision vs mastectomy) as well as radiotherapy. The aim is indeed to explore the impact of each treatment separately (different categories) and present potential associations between therapies and QoL and intrinsic capacity parameters. In standard clinical practice, these are managed through a “one-size-fits-all” approach, but CARDIOCARE, focusing on personalization of care, may ultimately change that.

Indeed, different pharmacological interventions can cause different types of cardiotoxicity and side effects, hence varying the impact on QoL. Data on the individual impact of the different types of systemic cancer therapy on intrinsic capacity are scarce, and the CARDIOCARE platform provides a unique opportunity to explore this as aggregated data and separately.

Thus, the CARDIOCARE prospective study will adopt technologically advanced tools to collect a large amount of data on the physical, psychosocial, and behavioral parameters of older patients with breast cancer to better identify patients at risk of developing cardiotoxicity due to oncological treatments and improve their psychological and physical well-being during and after their oncological care pathway.

Monitoring technologies based on sensors, wearables, eHealth (ePsycHeart and eHealtHeart), and a mobile app are used to collect patient-reported data; engage patients in their ongoing health and behavior; and make an impact on the communications between patients and clinicians in a closer, more trusting environment.

The mobile app is structured in 2 different main sections: the ePsycHeart app and the eHealtHeart app. This app is used during the first 6 months of the study to collect psychological, social, and physical variables.

The ePsycHeart section has been developed with a patient-oriented approach aiming to easily monitor and inform patients and physicians on the patients’ overall emotional, functional, and physical well-being by means of smart recommendations and on the most adequate intervention activity (eHealtHeart), tailored based on the output originated from ePsycHeart. In particular, ePsycHeart will contain different validated and standardized questionnaires to assess psychological, social, and physical variables.

The eHealtHeart section includes the main interventions, developed in modules to counteract dispositional, emotional, and behavioral risk factors for cardiotoxic effects and lower QoL after cancer therapy. Specifically, eHealtHeart will deliver effective interventions to prevent and delay progression of cardiotoxicity by targeting (1) the improvement of psychocognitive well-being, (2) the improvement of mobility and vitality, (3) the management of age-associated conditions (eg, urinary incontinence), (4) the prevention of falls, and (5) support for caregivers. The eHealtHeart main modules focus on several aspects.

One of the modules targets psychological well-being, with interventions on depression, emotional and dispositional states, and stressors based on a number of intervention tools. The first tool is biofeedback, which is a well-established method for collecting the user’s physiological parameters to foster better outcomes in health care, understanding the disease and delivering treatment. More specifically, through noninvasive external sensors, biofeedback gives constant real-time feedback to the user about parameters such as heart rate (HR). This feedback allows the patient to gain awareness and learn how to self-regulate their own bodily reactions, which are usually unconscious and automatic, through individualized approaches that improve one’s adaptability to physiological responses [11,12].

The second tool is the best possible self (BPS) activity, which was introduced by King [13] as a disclosure exercise in which participants write about their life goals and priorities imagining themselves in the future once everything has turned out for the best. Participants will be asked to carry out this task for 4 or 5 days every month for the first 6 months of the study. BPS is a writing paradigm developed to help participants set goals and priorities for a positive, imagined future [14], with strong evidence of improving mental and physical well-being.

The third tool is expressive writing, a cost-effective therapeutic intervention in which individuals are asked to write for approximately 15 to 20 minutes about a major life event or traumatic experience over 3 or 4 consecutive days. Research has reported reductions in biological indicators of stress and stress-related conditions affecting blood pressure, sleep, depression, immune function, and pain [15].

The fourth tool is ABCDE, a method in which each participant is asked to think about an adversity (A) that happened during the last period. The participant is then asked to return to the thoughts they had while facing the adversity and reflect on their own beliefs associated with that adversity (B). Successively, the participant is invited to focus on the consequences (C) of their beliefs in terms of experimented feelings and actions taken. After that, the participant needs to dispute (D) the beliefs, meaning that the person’s beliefs will be attacked and questioned. Finally, the last step is called Energy I, and it helps the participant observe the connection between the thought (B) and the consequences (C). This last step should help the participant gain awareness about the fact that pessimistic thoughts lead to negative reactions and emotions, whereas positive beliefs lead to positive outcomes regarding one’s own feelings as well as environmental consequences.

Another eHealtHeart module focuses on cognitive stimulation and training via find the word, tic-tac-toe, color beans, and drawing exercises. Every 6 months, the cognitive effect of these exercises on patients will be assessed.

Improvement of mobility and vitality are addressed by another eHealtHeart module. The physical activity and exercise module offers a collection of different graphs, such as bar, line, and pie charts, that will represent data collected through a physical activity–tracking device. The monitoring of steps, duration of sleep, and daily summaries (exercise, type of activity, average HR, and stress level) will be presented to inform patients and physicians about the overall functional well-being of the patient.

Sensory screening is also conducted in the eHealtHeart main modules. A vision test that follows the Snellen test guidelines will be available. The patient must keep the mobile phone screen at a certain distance and, by closing each eye, must assess the letters that the mobile app shows. At the end, an overall score is provided based on the patient’s answers. The Snellen test can be repeated as many times as the patient wants within a day. A hearing test that follows the whisper test guidelines will also be available. The procedure will play back certain sounds from the left to the right side of the smartphone speakers. On the basis of what the patient heard and did not hear, an overall score with scaling is provided. The whisper test can be repeated as many times as the patient wants within a day.

The eHealtHeart main modules also promote the management of geriatric syndromes. In the Incontinence Management module, a patient will be able to report urination incidents, follow instructions to exercise the pelvic muscles, and add reminders regarding pelvic floor exercises. The urination data will be stored on the CARDIOCARE server and will be available to the patient and the patient’s assigned health care professional. Furthermore, the patient will be prompted to exercise their pelvic floor muscles with the help of instructions and visual aids. The pelvic floor exercises have different difficulty levels (regarding, eg, repetitions and time).

A fall detection and fall prevention module will be available on the app. The system, using sensors from the mobile device, will try to detect whether the patient had a fall incident and will inform the caregiver to communicate with the patient. Furthermore, educational material containing guidelines and videos for fall prevention will be available to the patients.

On the first day of recruitment, each patient receives a mobile phone (with the CARDIOCARE app), a smartwatch, and a belt from their clinical center to be used during the first 6 months of the study. Details on the frequency and duration of the interventions are provided in Table 1.

**Table 1 table1:** Frequency of the interventions of the eHealtHeart mobile app.

Module and interventions		Frequency
**Psychological well-being measured until month 6**		
	Biofeedback	If the patient reports a high anxiety and depression value in the ePsycHeart section (PHQ-4^a^), an alert will suggest to complete the module.
	BPS^b^	20 minutes each day for 4-5 consecutive days every 3 months starting 1 month after baseline
	EW^c^	20 minutes each day for 4-5 consecutive days every 3 months starting at baseline
	ABCDE^d^	Every 3 months starting 2 months after baseline
**Cognitive stimulation and training**		
	Find the word Tic-tac-toe Color beans Drawing	5 consecutive days per month until month 6
**Improvement of mobility and vitality**		
	Physical activity and exercise	At least 48 continuous hours each week until month 6
**Sensory screening**		
	Vision test Hearing test	At baseline and at month 6
**Management of geriatric syndromes**		
	Pelvic floor exercises	Daily for 3 months
	Fall detection and fall prevention	Twice a week for 6 weeks

^a^PHQ-4: 4-item Patient Health Questionnaire.

^b^BPS: best possible self.

^c^EW: expressive writing.

^d^ABCDE: activating event or situation, beliefs, consequences, disputation of beliefs, and effective new approach.

### Objectives and Rationale

The objectives and rationale of this prospective clinical study are as follows:

To stratify patients aged ≥60 years with breast cancer based on their risk of developing cardiotoxicity. The rationale is that, so far, multiple studies have explored the effects of specific risk factors; however, these studies have yet to deal comprehensively with the impact of clinical, biological, psychological, and behavioral risk factors and their interactions.To evaluate the effects of eHealth psychological and behavioral interventions on the intrinsic capacity and QoL of older patients with breast cancer and on their risk of developing cardiac toxicity. The rationale is that, although recent studies associate psychosocial and behavioral characteristics with the risk of developing cardiovascular diseases, these studies on older patients with breast cancer are still limited [16]. However, gaining such knowledge is necessary to generate hypotheses on using eHealth interventions to support this clinical population.

The primary study end point is to evaluate and monitor the onset of cardiotoxicity, where subclinical cardiotoxicity is defined as preserved left ventricular ejection fraction (LVEF; ie, LVEF≥50%) with >15% reduction in global longitudinal strain relative to the baseline or new rise in cardiac troponin I or natriuretic peptide levels in plasma and clinical cardiotoxicity is defined as the reduction in LVEF by ≥10% from baseline to a value of <50% at any time point during study follow-up [17,18].

Secondary end points include intrapatient assessment of major adverse cardiovascular events (MACEs) [19,20] (angina pectoris, acute myocardial infarction, major ventricular arrhythmias, pacemaker implantation, acute heart failure [New York Heart Association class 4], acute ischemic brain disease with neurological persistence evidence, and severe hypertension requiring treatment with angiotensin-converting enzyme or β-blockers), intrapatient assessment of plasma troponin I levels during the follow-up and their association or agreement with LVEF, intrapatient assessment of plasma brain natriuretic peptide elevation, hospital admissions due to cardiovascular causes or falls, cardiovascular death, noncardiovascular death, and health-related QoL (assessed using the European Organisation for Research and Treatment of Cancer Quality of Life Questionnaire–Breast Cancer, a validated breast cancer patient-reported outcome measure).

Secondary end points also include the cost-effectiveness of provided health care pathways, determined through costs combined with quality-adjusted life years (QALYs). Costs will consider health care provided, numbers of admissions and days spent in hospital, and patient costs for out-of-pocket expenses associated with their condition (ie, travel expenses [of both the patient and caregiver], over-the-counter medicines and supplements, complementary therapies not supported by the health care system, home help, and time away from work).

Psychological and behavioral variables will also be measured as secondary end points. Intrinsic (mental and physical) capacity will be evaluated through the comprehensive geriatric assessment using standardized patient-reported outcome measures where applicable, sensors and wearables, and performance tests. More specifically, the following variables will be measured—(1) mobility and locomotion (distance, balance, and gait speed), (2) sensory ability (Snellen test and whisper test), and (3) vitality status (exercise, electrocardiogram, HR variability, grip strength, nutritional or energy state, sleep, and fatigue)—together with a complementary frailty screening (using the Geriatric 8 frailty screening tool, declared as the preferred tool by the International Society of Geriatric Oncology for identifying frailty in older patients with cancer, including patients with breast cancer) and frailty assessment (comorbidity, mental health, cognition, functional status, polypharmacy, geriatric syndromes, and socioeconomic and nutritional status). Other psychological and behavioral variables measured are psychocognitive status (personal traits, cognitive factors, and emotional states), social and socioeconomic factors, and general QoL, measured using standardized validated questionnaires to make comparisons with the more specific psychological and behavioral measures listed previously.

The following continuous variables will also be measured to identify predictive factors of disease trajectories and cardiac toxicity related to the objective of developing, refining, and validating the risk stratification model. Imaging markers of cardiac structural and functional variables will be measured using echocardiography, including LVEF percentage (Simpson biplane method [left ventricle end-diastolic volume and left ventricle end-systolic volume]), left ventricular diastolic dysfunction+left ventricular systolic dysfunction, interventricular septal end diastole, left ventricular posterior wall end diastole, fractional shortening percentage, mass index+relative wall thickness, tricuspid annular plane systolic excursion+S′ tricuspid annulus, left ventricular outflow tract velocity time integral+left ventricular outflow tract maximum velocity+aortic velocity time integral+aortic maximum velocity+aortic dimension, early to late diastolic transmitral flow velocity+medial early diastolic mitral annulus velocity +systolic-to-diastolic duration ratio, maximal tricuspid regurgitation velocity, right atrial pressure, left atrial volume index+right atrial volume index, global longitudinal strain (of both ventricles if possible), and myocardial work (global work index, global constructive work, global wasted work, and global work efficiency if available)+systolic and diastolic pressure. In addition, 2D echocardiographic sequences (grayscale images or videos of at least one representative full cardiac cycle) will be extracted as Digital Imaging and Communications in Medicine (DICOM) files for 3 different views (4 chambers, 3 chambers, and 2 chambers); independent 2D grayscale static images at end-diastole and end-systole frames will be extracted as DICOM files for each view; and corresponding manual annotations of the left ventricle (or left endocardium), left epicardium, and left atrium will be extracted from a subset of the aforementioned provided images.

Mammography DICOM images corresponding to the left mediolateral oblique view, right mediolateral oblique view, left craniocaudal view, and right craniocaudal view (conventional or tomosynthesis) will be obtained if the patient did not undergo mastectomy.

Other continuous variables that will be measured are whole-blood and plasma biomarkers, including biochemical (troponin I and brain natriuretic peptide), inflammatory and psychological (eg, if available, interleukin-6, tumor necrosis factor, HR variability, C-reactive protein, fibrinogen, and ferritin), and omics (single-nucleotide polymorphisms and extracellular vesicle micro-RNAs) biomarkers, and microbiome biomarkers from metagenomic analysis of stool samples (species diversity indexes; relative abundance at the family, genus, and species levels; and presence of pathogenic species).

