**Figure 1 figure1:**
[figure not shown]
Study design. BNP: brain natriuretic peptide; FU: follow-up; PREM: patient-reported experience measure; PROM: patient-reported outcome measure; QoL: quality of life; SNP: single-nucleotide polymorphism.

Great attention has been paid to the standardization of procedures among the clinical centers involved. Specifically, the inclusion criteria for the study are thoroughly detailed and are consistent across all 6 clinical centers involved in recruitment. This ensures that the same standards are followed at each site, allowing for a homogeneous participant selection process.

In addition, the technical partners involved in the study are responsible for continuously monitoring the data entered into the eCRF. They actively identify any values that may require further scrutiny or validation, ensuring the quality and integrity of the data.

Furthermore, the CARDIOCARE platform plays a crucial role in the standardization process. It provides real-time monitoring of whether patients are adhering to the prescribed activities according to the study protocol. If any discrepancies are detected, the clinical centers can contact their patients to address any issues, ensuring that all sites are aligned with the study protocol.

Therefore, while working across multiple centers presents certain challenges, the combination of detailed inclusion criteria, constant monitoring through eCRFs, and checks via the CARDIOCARE platform makes the process both feasible and practical. This multilayered approach allows for high levels of standardization and consistency across all sites.

Potential sources of bias have been minimized as follows. Regarding recall bias, the same questions are asked in both groups, ensuring that the bias is homogeneous, and reminders are sent to patients to complete the questionnaire on time. Regarding selection bias, the inclusion criteria are stringent, and all suitable candidates are enrolled by the centers. Regarding confirmation bias, the primary end points and most secondary end points are quantitative, reducing the likelihood of interpretation errors. Regarding observation bias, some questions are repeated across questionnaires, and patients complete the same questionnaire 3 to 5 times during the study.

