#### Exclusion Criteria

The exclusion criteria are age of <60 years and a diagnosis of severe psychiatric or neurological disorders that might impair the ability to provide informed consent.

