### Potential Limitations

This study’s psychological and behavioral monitoring is based on the use of a mobile app and wearable sensors, which may be problematic for some older adult users who are not familiar with or proficient in the use of this type of technology. Assistance and training in the use of the technology are provided at the recruitment stage, but the continued engagement with the app over the study period and compliance with the use requirements could pose significant obstacles to data collection. To circumvent this problem, the implementation of the study protocol includes frequent interaction between clinical staff and participants, as well as encouraging the involvement of family members to assist in maintaining compliance with the study protocols. This may result in a bias introduced by the level of technological dexterity of the patient, support in this regard from family members, or willingness to initiate communication with and seek help from clinical staff.

In addition, as with all multicenter studies, the study protocol is strictly applied and monitored at each clinical center to maintain consistency between centers. All equipment (eg, mobile phones and wearables) is the same and is provided through the CARDIOCARE project. Assessments of cardiotoxicity and subclinical cardiotoxicity are performed by a consensus group of cardiologists from each clinical center using all the available blood tests, echocardiograms, and treatment and patient history data. However, differences between populations, cultures, and environmental factors will be considered in the analysis plan to minimize any inherent bias.

Finally, a potential limitation of this project concerns the fact that the study follow-up period is limited to 12 months from the enrollment date to encompass both acute and early (within the first year) cardiotoxicity, defined based on imaging and biological biomarkers. Late cardiotoxicity (occurring up to several years after treatment) is not considered in this study.

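### The two-part definition of cardiotoxicity leaves a gap: a strain fall above 15% stops counting once LVEF drops below 50% by less than 10%, and the unit of that 10% is not stated

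*Protocol article*

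**What the plan says.** Under Objectives and Rationale the protocol article states: "The primary study end point is to evaluate and monitor the onset of cardiotoxicity". It then defines two categories.

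- Subclinical: "subclinical cardiotoxicity is defined as preserved left ventricular ejection fraction (LVEF; ie, LVEF≥50" per cent), joined to the markers "with >15% reduction in global longitudinal strain relative to the baseline or new rise in cardiac troponin I or natriuretic peptide levels in plasma".
- Clinical: "clinical cardiotoxicity is defined as the reduction in LVEF by ≥10% from baseline to a value of <50" per cent, at any time point in follow-up.

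Strain is explicitly measured relative to baseline. The 10% fall in LVEF, itself a percentage, carries no unit.

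The Selection Criteria set no lower limit on LVEF at entry: "The exclusion criteria are age of <60 years and a diagnosis of severe psychiatric or neurological disorders" that could impair consent.

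Under Statistical Considerations Regarding the Design, the effect on the primary end point is analysed with a Cox model, so the first qualifying visit fixes each woman's event and its time.

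**The concern.** A composite of this kind should classify every combination of LVEF, strain and biomarkers, and a worse state should never be scored as milder than a better one. Here the strain criterion carries an upper-range LVEF condition, while the LVEF criterion carries its own minimum fall. A woman can lose the first without gaining the second.

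Three things follow for the Cox analysis. Some onsets would be missed or dated late. The same measurements could be an event or a non-event, depending on how the analyst reads the 10% and the word *or*. And the Study Design section relies on the claim that "the primary end points and most secondary end points are quantitative, reducing the likelihood of interpretation errors", which holds only if the numbers classify every case.

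**Working it through.** No figure in the plan depends on this point. The sample size of 736 was set on raised troponin I at an assumed 21% incidence, without reference to LVEF. The check is therefore whether each pair of baseline and follow-up LVEF falls under a definition.

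**Inputs**, all from Objectives and Rationale: the subclinical condition LVEF ≥50%, a strain fall >15%, a new biomarker rise, and an LVEF fall ≥10% to <50%.

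**Two ambiguities, hence four readings**

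- The 10% is in points (b − f ≥ 10) or relative ((b − f)/b ≥ 0.10), where b is baseline and f is follow-up LVEF.
- The LVEF condition governs strain and biomarkers (condition on all), or strain only, so that a biomarker rise counts alone (condition on strain).

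**Worked cases**, each with a strain fall above 15%

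| LVEF, biomarker | Points, condition on all | Points, condition on strain | Relative, condition on all | Relative, condition on strain |
|---|---|---|---|---|
| 52→50, no rise | event | event | event | event |
| 52→48, no rise | neither | neither | neither | neither |
| 52→48, rise | neither | event | neither | event |
| 55→48, no rise | neither | neither | event | event |
| 55→48, rise | neither | event | event | event |

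Arithmetic: 52→48 is 4 points and 4/52 = 7.7%; 55→48 is 7 points and 7/55 = 12.7%.

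The first two rows show the defect without any dependence on reading: same baseline, same strain fall, lower LVEF, and the event disappears.

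**Extent of the gap for strain-only cases**, whole-number baselines of 50% or more, follow-up below 50%

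- Points: f runs from b − 9 to 49, which is 59 − b values. For b = 50 to 58 that is 9 + 8 + 7 + 6 + 5 + 4 + 3 + 2 + 1 = 45 pairs. The last is 58→49 (9 points).
- Relative: f must exceed 0.9b. For b = 50, 51, 52, 53, 54 that gives 4 + 4 + 3 + 2 + 1 = 14 pairs. The last is 54→49 (5/54 = 9.3%). At b = 55 the gap closes, since 55→49 is 6/55 = 10.9%.

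So 45 − 14 = 31 pairs change status with the unit alone. These are counts of possible pairs, not of patients.

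**Low LVEF at entry.** A woman who enters below 50% and stays there cannot meet the strain criterion, because its LVEF condition fails at every visit. Under the condition-on-all reading she cannot meet the biomarker criterion either.

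**The case against.** The strongest reply is that this is a narrow wording gap.

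- It works visit by visit. Echocardiography and biomarkers are scheduled about every three months, and a woman who met a criterion earlier has already had her event. This stands: the gap does not make her event-free for the whole study.
- A concurrent biomarker rise closes the gap if that clause stands alone. This stands for that reading, but leaves the strain-only case open.
- The Results section says that the amended definition of cardiotoxicity also includes MACEs, although Objectives and Rationale lists them as secondary. A MACE might therefore count. A change in LVEF or strain alone is not on the MACE list.
- Assessment is "performed by a consensus group of cardiologists from each clinical center using all the available blood tests, echocardiograms, and treatment and patient history data". Clinicians may classify such a woman sensibly, but no rule is given for the case.
- The definition cites sources, and the full protocol is not shown. Finer derivation detail may well be there. The article's own rule, however, gives a wrong ordering as written, which is more than an omission.

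A reader might infer three stronger points that the documents do not support. First, that a large share of women falling below 50% is lost: there is no LVEF distribution from which to compute this, and a woman with a small fall but no strain or biomarker change would remain a non-event under the fix below as well. Second, that 55→48 with a troponin rise meets neither definition: that is so on only one of the four readings. Third, that panels who know the arm would fill the gap with bias: allocation is made through the eCRF, but allocation is not listed among the data the assessors use, and the wording allows a single group drawn from all centres.

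**Conclusion.** The gap is real on the text and does not depend on interpretation for strain-only cases: LVEF below 50% after a fall of less than 10%, with a strain fall above 15% and no biomarker rise, is unclassified at that visit, while the same strain fall at LVEF 50% is an event. How far it extends to biomarker rises depends on how the sentence is parsed. For women with baseline LVEF below 50% the strain criterion is out of reach as long as LVEF stays there. The unstated unit decides whether baselines up to 58% or only up to 54% are exposed.

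The number of women affected cannot be derived. It is limited by earlier qualifying visits and, on one reading, by biomarker rises. The rule is the same in both arms, and nothing in the documents shows that the gap favours one of them; the demonstrable harm is missed or late events and a classification that analysts could apply differently. It should be corrected because the correction is cheap, not because a large effect has been shown.

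**What to change.** Define the primary event as the first visit that meets any one of the protocol's existing criteria, whatever the LVEF at that visit:

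- a fall in global longitudinal strain above 15% relative to baseline;
- a new rise in troponin I or natriuretic peptide;
- an LVEF fall of at least 10 to below 50%, with points or relative per cent stated.

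Keep clinical and subclinical as descriptive labels only. Derive the event by algorithm from the eCRF values, and record the change before the eCRF is frozen. Under this rule 52→48 with a strain fall becomes an event, and 52→48 with neither strain nor biomarker change stays a non-event, now by explicit rule.

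The cost is a revised definition and one derived variable, using data already scheduled. The event count may rise slightly, and the wording departs from the present two-category definition, which should be said when results are compared with studies that use it.
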